##### Social network (two measures)

The Lubben Social Network Scale - Revised (LSNS-R) is designed to measure social isolation in older adults through perceived support from family and friends [26]. The Practitioner Assessment of Network Type (PANT) [27, 28] allocates participants to one of five types of network reflecting their contact with family, friends and neighbours. The person with dementia completes both measures.

#### Secondary outcome measures for carers

##### Quality of life (two measures)

Carers complete both the ICECAP-O [20] and CASP-19 [21, 22] as summarised above.

##### Sense of competence

The Short Sense of Competence Questionnaire (SSCQ) enables carers to assess their own competence to cope with the person with dementia [29].

##### Mental health

The self-completed General Health Questionnaire (GHQ-12) will be used to identify minor psychiatric morbidity in carers [30].

#### Economic measures

##### Resource use (two measures)

The Client Service Receipt Inventory (CSRI) is a template used extensively in studies of mental health and dementia to record details of formal services received [31]. This is supplemented by study-specific measures of participants’ use of equipment, adaptations and ambulances (formal support). The Resource Utilisation in Dementia questionnaire (RUD) complements the CSRI by estimating the volume, duration and cost of support from formal and informal carers. People with dementia and carers complete both measures [32].

##### Health-related quality of life

The Euroquol 5-dimension 5-level questionnaire (EQ-5D-5 L) provides a simple descriptive profile that generates a single utility value for health status to assess quality of life [33, 34]. The person with dementia and the carer completes this scale.

#### Other data collected

##### Socio-demographic information

Interviewers collect socio-demographic data from both the person with dementia and the carer.

##### Study-specific measures

Interviewers collect data on comorbidities in the person with dementia, current use of memory aids and current medication. They also assess how confident they are about participants’ allocation to the trial groups.

##### Serious adverse events

In accordance with Good Clinical Practice all data collectors are encouraged to report deaths and adverse events that are life threatening, require or extend hospitalisation, result in disability or incapacity or are otherwise significant.

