### Intervention

The manualised intervention adds specialist equipment and advice by trained DSPs to TAU. It provides up to 6 hours contact with a DSP for the person with dementia and the identified carer (jointly referred to as participants). DSPs design and deliver a package of memory aids up to a maximum of £150 for the person with dementia to use at home. The package for each depends on their needs, preferences and existing use of memory aids. DSPs also advise on improving everyday memory skills and on using these aids to reduce memory lapses. The follow-up sessions address queries from participants and record whether aids are appropriate to the identified goals and needs and used accordingly. Further details about the implementation of the intervention are provided in Fig. 2.

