#### Treatment as usual

TAU comprises help from memory clinic staff, post diagnostic counselling and advice, and specialist follow up as appropriate. Participants in the comparator group also receive a general guide to dementia for patients and carers [13].

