### Procedure

#### Data collection

Interviewers, who are masked to the allocated group, interview participants face to face at home at baseline and 13 and 26 weeks after first interview. Data quality will be promoted in two ways: interviewers undertake online training (focussing on completing outcome measures) and sites check all documents to minimise missing data.

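### Serious adverse event reporting is worded as encouragement rather than a requirement, and because only the intervention arm has practitioner contact between the shared interviews, events may be under-recorded and possibly recorded unequally

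*Protocol article*

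**What the plan says.** The reporting rule is a single sentence in the Protocol article, section Serious adverse events. It invokes Good Clinical Practice and says that "all data collectors are encouraged to report deaths and adverse events that are life threatening". It then extends to admissions or longer hospital stays, disability, and anything else significant.

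Contact after randomisation differs between arms:

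- **Both arms.** Under Data collection, masked interviewers "interview participants face to face at home at baseline and 13 and 26 weeks after first interview".
- **Intervention arm only.** Under Intervention: "It provides up to 6 hours contact with a DSP for the person with dementia and the identified carer". Of the later visits it says: "The follow-up sessions address queries from participants and record whether aids are appropriate to the identified goals and needs". Random allocation puts the first DSP visit about 2 weeks after allocation.
- **Comparator arm.** Under Treatment as usual: "Participants in the comparator group also receive a general guide to dementia for patients and carers". No DSP contact is described.

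Under Resource use, both arms complete the Client Service Receipt Inventory (CSRI), used to "record details of formal services received", with study-specific items that include ambulance use. Governance arrangements says the trial follows the trials unit's standard operating procedures, which are not shown. Masking allows allocation to be disclosed when a serious adverse event occurs.

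**The concern.** The sentence appeals to a formal standard and then asks for less than a duty. A reader cannot tell from it whether a death or admission that a data collector learns of has to be recorded. If recording is discretionary, some events can be lost.

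The second issue is who hears of events. Intervention pairs have an additional set of staff contacts that comparator pairs do not. DSP sessions generate records, and the Process evaluation section collects data from DSPs, so the phrase covering all data collectors can reasonably be read to include them. If it does, unmasked staff who see one arm only feed the event count. A difference in counts would then mix event rates with intensity of contact: a spurious excess could appear in the intervention arm, or a real one could be dismissed as closer observation.

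The common route also has a weak spot. The Sample size section allows for 25% attrition by the final interview. A pair that misses an interview gives neither interview data nor CSRI data at that point, and pairs affected by death or serious illness are plausibly among them.

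**Working it through.** The documents give no serious adverse event rate, no capture probability and no safety power calculation, so there is no stated figure to reproduce. What can be checked is how large a spurious difference the described contact pattern could create, and under what conditions.

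**Inputs**

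- Pairs per arm: 480 / 2 = 240 (recruitment target, Sample size section). This only scales the counts; the ratio below does not depend on it.
- True risk of a serious event, *r*, equal in both arms: assumed.
- Probability that an event is recorded through the route shared by both arms, *a*: assumed, 0.5 to 1.0.
- Share of otherwise missed events picked up through DSP contact, *b*: assumed, 0 to 0.5.

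**Formulas**

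- Comparator capture = *a*
- Intervention capture = 1 − (1 − *a*)(1 − *b*)
- Apparent risk ratio = [1 − (1 − *a*)(1 − *b*)] / *a*. The true risk *r* cancels.

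**Results, no true difference between arms**

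| *a* | *b* = 0 | *b* = 0.25 | *b* = 0.5 |
|---|---|---|---|
| 0.5 | 1.00 | 0.625 / 0.5 = 1.25 | 0.75 / 0.5 = 1.50 |
| 0.7 | 1.00 | 0.775 / 0.7 = 1.11 | 0.85 / 0.7 = 1.21 |
| 0.9 | 1.00 | 0.925 / 0.9 = 1.03 | 0.95 / 0.9 = 1.06 |
| 1.0 | 1.00 | 1.00 | 1.00 |

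**One case in counts.** With *r* = 10%, each arm has 240 × 0.10 = 24 true events. With *a* = 0.7 and *b* = 0.5, the comparator arm records 24 × 0.7 = 16.8 and the intervention arm 24 × 0.85 = 20.4. Both arms are under-counted, and the ratio is 1.21.

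**What the table shows.** Unequal counting needs two things together: incomplete capture on the shared route (*a* below 1) and DSPs passing on events (*b* above 0). Remove either and the ratio is exactly 1.00. Under-counting needs only the first.

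**Reach of the shared interviews.** The Sample size section plans for 480 − 360 = 120 pairs without final data. Any safety count that relies on interviews alone would miss events in those pairs unless they came to light another way.

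**The case against.** The strongest reply is that this is a condensed article. Event forms, reporting duties and standard questions usually sit in the full protocol and the trials unit's procedures, neither of which is shown, so their absence here proves nothing. That is right, and the point does not rest on that absence. It rests on a rule the article does state. If the unseen procedures make reporting mandatory, the published sentence misdescribes the trial; if they do not, the weakness is real. The sentence should change in either case.

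A reader might go further and infer that serious events are captured only when someone chooses to report them, that harms are under-counted, and that they are counted unequally. The documents do not support that:

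- The article does not say that encouragement is the only route.
- It does not name DSPs as reporters of adverse events; their sessions are described as dealing with queries and with how aids suit and are used.
- Both arms have the same masked interviews and the same service-use measures. Usual care, with memory clinic staff and specialist follow-up as appropriate, gives sites a way to learn of events in either arm.
- No capture rate is given, so any single risk ratio is only one assumed case.

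It is also fair to say that the article describes no formal between-arm comparison of serious events, that the primary outcome is untouched, and that memory aids and advice are a low-risk intervention by nature. These points limit the severity. They do not justify leaving the reporting of deaths and admissions worded as optional.

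**Conclusion.** The point holds as a weakness of wording with a possible consequence, not as a demonstrated bias. Encouragement is too weak a term for a sentence that invokes Good Clinical Practice, and it leaves capture to discretion. Events may therefore be under-recorded. They may also be recorded unequally, on two conditions that the article leaves open: that DSPs report events, and that capture on the shared route is incomplete. With shared capture of 50% to 100%, and DSP contact recovering none to half of what is missed, the apparent risk ratio with no true difference lies between 1.0 and 1.5; at 90% shared capture it is at most 1.06. All of these inputs are assumptions.

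Severity is minor to moderate. The Bristol Activities of Daily Living Scale analysis is not affected; what is at stake is whether the safety counts can be interpreted.

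**What to change.** 1. In the Serious adverse events section, replace the encouragement with an obligation: data collectors *must* report.
2. Have the masked interviewers put one fixed checklist, covering the categories already listed in that section, to both arms at 13 and 26 weeks.
3. Cross-check hospital admissions recorded as serious events against the CSRI, and resolve mismatches.
4. For pairs who miss an interview, obtain deaths and known serious events from the site, by the same procedure in both arms.
5. Report every event to the data monitoring committee, flag those known only through DSP contact, and show the between-arm counts with and without them.

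Restricting the comparison to events elicited at interview would look cleaner but is not advisable. It would drop events in pairs never re-interviewed, which is why items 4 and 5 are needed.

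The cost is a short checklist within interviews already planned, a reconciliation listing, and a site enquiry for pairs lost to interview; no extra visits are needed. There will be more reports to process, many unrelated to the intervention. There is also a small added risk of unmasking interviewers, because serious adverse events are one of the permitted grounds for disclosing allocation.

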### Procedure

#### Data collection

Interviewers, who are masked to the allocated group, interview participants face to face at home at baseline and 13 and 26 weeks after first interview. Data quality will be promoted in two ways: interviewers undertake online training (focussing on completing outcome measures) and sites check all documents to minimise missing data.

#### Random allocation

The Trial Manager (TM) coordinates recruitment from all sites and forwards details to STU through their email-based randomisation service. After baseline interviews, the unmasked Trial Data Manager (TDM) at STU oversees stratification of people with dementia by Trust, age, gender, whether living with a carer and time since first attendance at memory clinic or equivalent. Allocation between intervention and comparator groups using dynamic software randomises participants in real time, thus preventing subversion while ensuring (stochastic) balance between the two groups [35].

The person with dementia receives a letter specifying their allocated group and reminding them what this entails. Those in the comparator group receive a general guide to dementia [13]. The intervention group receive confirmation of arrangements for an initial visit by the DSP after about 2 weeks.

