### Setting

The study runs in three National Health Service (NHS) Trusts in England, and more may follow. To be eligible participating Trusts must provide a memory service, a health-based resource providing early diagnosis and support for people with dementia and their carers. They must also identify a local Principal Investigator (PI), obtain support from their local Research and Development department and Clinical Research Network (CRN) to complete the research activities described in this protocol, and employ appropriately experienced persons as DSPs.

Participants will be recruited primarily from memory services. “Join Dementia Research,” an on-line self-registration service enabling volunteers with memory problems or dementia and their carers to register their interest in taking part in research, will also be used as a recruitment tool.

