### Statistical analysis

Analysis will follow a defined statistical analysis plan approved by the DMEC before data are accessed. Baseline characteristics of participants will be presented. Continuous variables will be reported by means and standard deviations and categorical variables by counts and percentages. Analyses by treatment allocated will estimate the effect of the intervention on participants, using analysis of covariance to adjust for baseline differences in demographic characteristics, comorbidities, time since first attendance at memory clinic or equivalent and for the interval until follow up. Primary analysis will focus on BADLS scores at 26 weeks. Secondary analysis will take account of the content of, and adherence to, the intervention to explore the effect of compliance on BADLS scores.

To explore whether people with dementia who have particular characteristics are more likely to use specific aids, logistic regression will be used. To identify which participants are more likely to benefit from this intervention, linear regression will be used to relate change in BADLS scores at 26 weeks to similar covariates.

Whether the inevitable missing data cause bias will be investigated. If predictors of missing data are identified that are related to outcomes, multiple imputation to adjust for these biases will be used.

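### The covariate list of the primary model omits Trust and does not name living with a carer, although both are stratification factors; if they predict BADLS, the test is mildly conservative

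*Protocol article*

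**What the plan says.** The Random allocation section has the trial data manager oversee "stratification of people with dementia by Trust, age, gender, whether living with a carer and time since first attendance at memory clinic or equivalent". That is five factors. The method is adaptive: "Allocation between intervention and comparator groups using dynamic software randomises participants in real time", and the section describes the resulting balance as stochastic. The Setting section adds: "The study runs in three National Health Service (NHS) Trusts in England, and more may follow".

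The Statistical analysis section says that effects will be estimated by allocated treatment, "using analysis of covariance to adjust for baseline differences in demographic characteristics, comorbidities", continuing with "time since first attendance at memory clinic or equivalent and for the interval until follow up". It then says: "Primary analysis will focus on BADLS scores at 26 weeks". The section opens by deferring to a further document: "Analysis will follow a defined statistical analysis plan approved by the DMEC before data are accessed". That plan is not shown.

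**The concern.** Balancing the groups on a prognostic factor makes the treatment estimate more precise. The analysis shows that precision only if the factor is in the model. If it is left out, its variance stays in the residual, the reported standard error exceeds the real one, intervals are too wide and the test rejects too seldom under the null.

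There is reason to ask about both factors. Each Trust runs its own memory service and employs its own support practitioners, so Trusts may differ in patients and in delivery. Carers rate BADLS, so living with the person may affect how much of their daily function the carer sees. The wording about adjusting for baseline differences adds a smaller uncertainty: it could be taken to mean adjusting only where the groups turn out to differ. Factors balanced by design would then be the least likely to be included.

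**Working it through.** **1. Factors against covariates**

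| Stratification factor (Random allocation) | In the covariate list (Statistical analysis)? |
|---|---|
| Trust | No. An organisation is neither a demographic characteristic nor a comorbidity |
| Age | Covered by demographic characteristics |
| Gender | Covered by demographic characteristics |
| Living with a carer | Not named; may or may not be covered by demographic characteristics |
| Time since first attendance | Named |

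So one factor is absent and one is unclear.

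**2. The plan's own figure**

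Inputs from Sample size: standardised difference 0.30, two-sided 5%, power 80%, 180 analysable per group, 25% attrition.

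- n per group = 2 × (1.960 + 0.842)² / 0.30² = 174.4, so 175 per group or 350 in all, against 360 stated.
- With 180 per group, SE = √(2/180) = 0.1054 and 0.30/0.1054 = 2.846. Power = Φ(2.846 − 1.960) = Φ(0.886) = 81.2%.
- 360/0.75 = 480 to be randomised, as stated.

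The figure reproduces as a plain two-group calculation. It takes no credit for stratification or covariates.

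**3. Effect of leaving the factors out**

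Let R² be the share of BADLS variance, after the other covariates, that Trust and living with a carer explain. The article gives no value, so this is an assumption, shown from 0 to 0.10. Put s = √(1 − R²) and take balance on the factors as exact:

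- overstatement of the SE = 1/s − 1
- type I error with the factors omitted = 2 × [1 − Φ(1.960/s)]
- power with the factors omitted = Φ(0.886/s)
- power with the factors included = Φ(2.846/s − 1.960)

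| R² | s | SE too large by | Type I error | Power, omitted | Power, included | Points forgone |
|---|---|---|---|---|---|---|
| 0 | 1.000 | 0% | 5.0% | 81.2% | 81.2% | 0 |
| 0.02 | 0.990 | 1.0% | 4.8% | 81.5% | 82.0% | 0.5 |
| 0.05 | 0.975 | 2.6% | 4.4% | 81.8% | 83.1% | 1.3 |
| 0.10 | 0.949 | 5.4% | 3.9% | 82.5% | 85.1% | 2.6 |

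**4. Check by simulation**

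Exact balance is the limiting case, so minimisation on five factors was simulated. The settings are assumptions: three Trusts of equal expected size, four binary factors, biased coin 0.8, n = 360, R² split equally between Trust and living with a carer, 4,000 runs per setting.

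- At R² = 0 the models with and without the two factors gave the same mean SE, 0.1053.
- At R² = 0.10 without the factors, the mean model SE was 0.1054 against an empirical 0.1020 under no effect (0.1054/0.1020 = 1.033), and 0.1053 against 0.1003 under an effect of 0.30 (1.050). That is about 3 to 5% too large. With the factors included, the model SE was 0.1000.
- Rejection under the null at R² = 0.10 was 4.5% without the factors and 5.7% with them. The Monte Carlo error is √(0.05 × 0.95/4000) = 0.34 points, so the conservatism is in the expected direction but less marked than the formula's 3.9%.
- Power at R² = 0.10 was 81.9% without and 84.5% with the factors.

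The formula values at R² = 0.10 are best read as an upper limit.

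**The case against.** The strongest reply is that this is a journal article that defers to an analysis plan approved before data access. Its covariates are given in broad classes and are not said to be exhaustive. Nothing says that Trust will be excluded. This stands to the extent that the unseen plan may already include Trust. It does not remove the mismatch, because the section is not silent: it repeats one stratification factor almost word for word, adds two covariates that are not stratification factors, and leaves Trust out.

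Three stronger readings are tempting, and the article does not support them.

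- A reader might infer that living with a carer is also missing from the model. The term demographic characteristics is not itemised, and socio-demographic data are collected from both members of the pair. If the term covers age and gender, it may cover living arrangement too.
- A reader might infer that the standard error is too large as a matter of fact. That holds only if the omitted factors predict BADLS given the other covariates. The article gives no figure for this, and at R² = 0 the effect is nil. If living with a carer is already covered, Trust alone would have to supply the R².
- A reader might infer that power built into the design is lost. The 80% was planned without credit for stratification, and power with the factors omitted stays at 81% or above throughout the table. What is forgone is a possible extra gain.

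**Conclusion.** The point holds as a mismatch of limited consequence. The stated primary model omits Trust, leaves living with a carer unclear, and so does not fully correspond to the allocation. If the two factors predict BADLS beyond the other covariates, intervals are somewhat too wide and the test is mildly conservative: by nothing at R² = 0, by about 1% of the SE at 0.02, and by at most about 5% at 0.10. The forgone power is between 0 and 2.6 points over that range. The treatment estimate is not biased and the type I error is not inflated. The planned 80% power is met given the 360 analysable pairs of the Sample size section. The sizes rest on an assumed R² and on near-exact balance; the mismatch itself rests only on the text.

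**What to change.** State in the Statistical analysis section that all five stratification factors (Trust, age, gender, living with a carer, and time since first attendance) enter the primary BADLS model whatever the observed balance. The coding of each factor can be left to the analysis plan. If that plan already lists all five, only the article's wording needs to be brought into line.

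The values are already held from randomisation, so no new data are needed. With three Trusts the added terms take 2 degrees of freedom for Trust and 1 for living with a carer, 3 in all out of about 360, and one more for each Trust that joins. The Trial status section reports that recruitment was under way, and the analysis plan is to be approved before data are accessed, so the change can be prespecified.
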